### Treatment

#### Control

Participants in the control group receive no medical rehabilitation and are identified through propensity score matching.

#### Intervention

Participants in the treatment group will take part in a medical rehabilitation programme based on current treatment standards and guidelines for the rehabilitation of back pain [34]. The medical rehabilitation programmes are multimodal and consist of three to 4 h of therapy per day, including sports and exercise therapy, physiotherapy, occupational therapy, massage and other physical therapies, social and psychological counselling, patient education, pain management and relaxation training. They focus on the functional limitations of the musculoskeletal system and aim to restore physical abilities in order to promote participation in work and daily life. The duration of the rehabilitation programme is determined initially by the GPI North and GPI Central Germany and is usually about 3 weeks. Rehabilitation services may be provided as inpatient or outpatient programmes. Patients with musculoskeletal diseases spend 23 days at the rehabilitation centre on average [44], with sports exercise being the most frequent therapy during the 3-week rehabilitation (>13 h per week, 74% of all therapies) [44]. The rehabilitation centre and the patient may arrange to extend the programme. The patient may stop the rehabilitation programme ahead of schedule on request.

Applications to use rehabilitation services, the related decisions, and the utilisation of these services are documented in the GPI registers and data relating to the first year of the study will be extracted from these records.

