## Methods

### Study design

The study is designed as a cohort study. Persons with back pain will be identified via a preliminary survey and then followed up. Back pain patients who complete a medical rehabilitation will be compared with back pain patients who do not participate in a medical rehabilitation programme. Propensity score matching will be used to match controls to treated patients and to estimate unbiased effects of medical rehabilitation.

Baseline data will be assessed to identify persons with back pain and to analyse barriers to using rehabilitation services. Follow-up data will be assessed at the beginning of the third year of the study to determine the effectiveness of medical rehabilitation. Administrative data from the GPI registers will also be used. Given the observational design no-one will be blinded before, during or after the trial.

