### Participants

Employed persons aged 45 to 59 years will be included. The exclusion criteria are having applied for or used medical rehabilitation services during the last 4 years and previous requests for or receipt of disability pension benefits. Samples will be drawn in equal proportions from the populations of the GPI North (*n* = 22,500) and GPI Central Germany (*n* = 22,500). The samples will be stratified by sex in a ratio of 1:1 and by sickness absence benefits in a ratio of 2:1 (less than 1 week of sickness absence benefits vs. at least 1 week of sickness absence benefits). In the first quarter of the first year, a baseline survey will be performed to assess the 3-month prevalence of back pain (i.e., back pain at any time during the past 3 months including today). The localisation of back pain will be represented on a pain drawing [1]. In accordance with previous large, epidemiological studies in Germany, back pain is defined as pain anywhere in the area between C7 and the gluteal folds [45–47]. Only persons who report some kind of back pain in the baseline survey will be followed in our prospective analysis.

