##### Sickness absence benefits and disability pensions

Data on days in receipt of sickness absence benefits, days in regular employment, applications for and granting of a disability pension will be extracted from the GPI registers during the third year of the study. These variables are the secondary outcomes in our analyses of the effectiveness of medical rehabilitation.

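### Rehabilitation records are specified for study year one only, but controls are defined without a time limit and the outcome comes in year three, so controls treated in year two cannot be identified

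*Protocol article*

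**What the plan says.** All references are to the protocol article.

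- **Exposure window.** The Intervention section covers applications, decisions and use of services together: "the utilisation of these services are documented in the GPI registers and data relating to the first year of the study will be extracted". The abstract names administrative records as the source for rehabilitation use. Table 2 lists no follow-up questionnaire item on it; former rehabilitation is asked at baseline only.
- **Group definition.** Under Control: "Participants in the control group receive no medical rehabilitation and are identified through propensity score matching". Under Study design: "Back pain patients who complete a medical rehabilitation will be compared with back pain patients who do not participate in a medical rehabilitation programme". Neither sentence carries a time limit, and Sample size estimation calls the controls untreated.
- **Timing.** Under Participants: "In the first quarter of the first year, a baseline survey will be performed". Under Study design: "Follow-up data will be assessed at the beginning of the third year of the study to determine the effectiveness of medical rehabilitation". The abstract dates the two surveys to 2017 and 2019.
- **Year-three register data.** The section on sickness absence benefits and disability pensions lists benefit days, employment days and pensions: "applications for and granting of a disability pension will be extracted from the GPI registers during the third year of the study". Rehabilitation is not on that list.
- **Barrier analysis.** The statistical section follows people through recognition of need, application, approval, participation and completion, and compares groups at each stage.

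**The concern.** About a year lies between the end of the stated exposure window and the outcome. During it, a person classed as a control can apply for, be granted and complete rehabilitation without the planned data showing it. The study could then not check its own statement that controls go untreated.

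Matching may sharpen the problem. It selects the non-users whose baseline characteristics most resemble those of users, so matched controls may be more likely than the average non-user to attend later.

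Two results are exposed:

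- **Effectiveness.** If rehabilitation is beneficial, later-treated controls pull the estimated difference towards zero. A small or null estimate could then be read as weak effectiveness when part of it reflects treated controls.
- **Barriers.** Someone who applies late in year one and is admitted in year two appears as an applicant who did not participate. Waiting time would then be mixed with genuine barriers at the later stages. This harm does not depend on any treatment effect.

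**Working it through.** **Step 1: reproduce the plan's figures.** Inputs from the abstract and Sample size estimation: 45,000 invited; 40% baseline response; 80% linkage consent; 40% back pain; 8% utilisation; 60% follow-up response; 1:3 matching; standardised mean difference (SMD) 0.2; two-tailed alpha 0.05.

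- Cohort: 45,000 × 0.40 × 0.80 × 0.40 = 5,760.
- Rehabilitants at follow-up: 5,760 × 0.08 × 0.60 = 276.
- Controls: 3 × 276 = 828.
- Power = Φ(SMD / √(1/276 + 1/828) − 1.96). The root is 0.0695, so Φ(0.2/0.0695 − 1.96) = Φ(0.918) = 0.82.

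The stated 0.82 reproduces. It presumes that all 828 controls are untreated.

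**Step 2: let a share c of controls be treated in year two.** Assume that they gain the full effect. The control mean then moves by c times the effect, so the observed SMD = 0.2 × (1 − c). The documents do not give c; the range is an assumption. The centre repeats the stated 8%, which itself has no stated period. The upper end is the 20% of controls who used rehabilitation within 6 months in the randomised trial described in the Background, a population selected for apparent need.

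| c (assumed) | Controls affected (of 828) | SMD | Power |
|---|---|---|---|
| 0% | 0 | 0.200 | 0.82 |
| 1% | 8 | 0.198 | 0.81 |
| 4% | 33 | 0.192 | 0.79 |
| 8% | 66 | 0.184 | 0.75 |
| 10% | 83 | 0.180 | 0.74 |
| 20% | 166 | 0.160 | 0.63 |

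Worked line for 8%: 0.2 × 0.92 = 0.184; Φ(0.184/0.0695 − 1.96) = Φ(0.687) = 0.75. Restoring the original power at 8% would take about 327 rehabilitants with 981 controls.

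**Step 3: set the windows side by side.**

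| Item | Study year 1 (2017) | Study year 2 (2018) | Start of year 3 (2019) |
|---|---|---|---|
| Baseline survey | yes, first quarter | – | – |
| Rehabilitation records | yes | none stated | none stated |
| Requirement that controls are untreated | applies | applies as worded | applies as worded |
| Primary outcome | baseline value | – | follow-up value |

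The second and third rows do not match for year two. No section shown describes censoring, exclusion or a sensitivity analysis for controls treated in that year.

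**The case against.** **A year-one exposure window is a legitimate design.** Comparing rehabilitation in year one with none in year one leaves about a year between treatment and outcome. That suits the stated interest in long-term effects and avoids defining groups by later events. Under that estimand, later use by controls is part of usual care and not bias. This stands. But the Study design and Control sections do not word the comparison that way, and year-two use would still have to be known to interpret the result.

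**The text does not say that extraction stops after year one.** A reader might infer a deliberate limit. The documents do not support that: the word only is absent, the schedule in Table 1 is not shown, and the year-three list belongs to a section on outcomes, where exposure data would not be expected. What stands is narrower: no visible section extends the window.

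**The size is not known.** A reader might infer heavy contamination because matched controls resemble users. Matching makes higher uptake plausible but does not fix its level. People who did not attend in year one may be persistently less inclined to do so, and late users may not have the full benefit by follow-up. At 1% to 4% the loss is small.

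**The bias is not built in.** A reader might infer that the control definition can never be met. The registers hold the missing records, so the gap can be closed.

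**Dropping later-treated controls could do harm.** The Background describes impaired health as the main predictor of rehabilitation use. Removing later users may therefore leave healthier controls and bias the comparison against rehabilitation. This stands, and it rules out simple exclusion as the primary rule.

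**The barrier effect is unquantified.** No waiting time is given, and the barrier section sets no cut-off of its own. That limits what can be said about size; the stated record window still ends the observable pathway with year one.

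**Conclusion.** The point holds as a mismatch in the text: a year-one record window, a control group defined without a time limit, and an outcome in year three. Followed as written, the plan cannot verify that its controls are untreated, and it cuts off the pathway of late year-one applicants.

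Dilution towards zero follows only if rehabilitation is beneficial, and the Background calls that evidence contradictory. With no effect there is nothing to dilute. With the planned SMD of 0.2 and full benefit in later-treated controls, power runs from about 0.81 to 0.63 as c goes from 1% to 20%, with 0.75 at 8%. The documents cannot say where in that range the study would fall. This is an inexpensive and worthwhile improvement, not evidence that the primary analysis is invalid.

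**What to change.** - **Data.** Add rehabilitation application, decision, start and discharge dates, from baseline to the follow-up survey, to the register extraction already planned for year three.
- **Estimand.** State the time frame in Study design and Control, for example rehabilitation in year one versus none in year one.
- **Reporting.** Give year-two rehabilitation use by matched group.
- **Sensitivity analysis.** Address later-treated controls, for example by censoring with weights or time-dependent matching. Do not make their simple exclusion the primary rule, because it conditions on events after baseline.
- **Barrier analysis.** Follow year-one applicants through to admission and discharge before classing them as non-participants or non-completers.

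The cost is a few extra register fields from the same source, a sentence or two in the protocol and some additional analysis work.

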**Methods:**

In 2017 a postal questionnaire will be sent to 45,000 persons aged 45 to 59 years whose pension insurance contributions are managed by the GPI North or the GPI Central Germany. In 2019 respondents who report back pain in the first survey (*n* = 5760 expected) will be sent a second questionnaire. Individuals will be eligible for the first survey if they are employed, have neither used nor applied for a rehabilitation programme during the last 4 years and neither received nor applied for a disability pension. The sample will be drawn randomly from the registers of the GPI North (*n* = 22,500) and the GPI Central Germany (*n* = 22,500) and stratified by sex and duration of sickness absence benefits. Barriers to rehabilitation services will be related to socio-demographic and social characteristics, pain and attitudes to pain, health and health behaviour, healthcare utilisation, experiences and cognitions about rehabilitation services and job conditions. Propensity score matched analyses will be used to examine the effectiveness of rehabilitation services. Data on use of medical rehabilitation will be extracted from administrative records. The primary outcome is pain disability. Secondary outcomes are pain intensity and days of disability, pain self-efficacy, fear avoidance beliefs, self-rated health, depression, healthcare utilisation, self-rated work ability and subjective prognosis of employability, sickness absence benefits, and disability pensions.

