### Recruitment

After the sample has been drawn potential study participants will be contacted by post by the GPI. The first mailing of the baseline survey will include a personalised cover letter, information about the study, a consent form, and two envelopes (a prepaid envelope and a small envelope for the consent form). The prepaid envelope is to be used to send the completed questionnaire and the envelope containing the consent form to the university. The project staff at the university will collect the consent form envelopes and pass them on to the relevant GPI employees without opening them, as they contain personal data. The GPI employees will check off those who have provided informed consent against a study list and inform the scientists at the university by transferring the identification numbers for consenting participants. Participation is voluntary and participants are free to withdraw their consent at any time without any consequences.

One, four and five weeks after the initial mailing of the questionnaire reminders will be sent to potential study participants. The first reminder takes the form of a short thank-you letter to remind the recipient about the study and the questionnaire they received recently. The second reminder is sent 3 weeks after the first reminder and contains all of the above-mentioned study material. This reminder is only sent to persons who have not yet returned their questionnaire. The third and final reminder is sent 1 week after the second reminder, once again it highlights the importance of the recipient’s participation in the study and thanks them in advance for their support. The final reminder also contains a link to the study website (www.rehab-bp.de) which will inform about the study and its findings.

During the third study year, a second survey will be conducted. The format is the same as for the first survey: a first mailing comprising a cover letter, questionnaire and prepaid envelope, a second mailing consisting of a short reminder, a third mailing containing the same material as the first, sent only to those who have not yet returned their questionnaires, and a fourth mailing consisting of a final short reminder. The schedule for enrolment, interventions and assessments is displayed in Table 1.

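### The register window for applications and rehabilitation contains the baseline survey period, and no rule requires either event to follow the person's own questionnaire

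*Protocol article*

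**What the plan says.** Under Treatment, Intervention, the article explains that the registers document applications, the decisions on them and use of services, and that "data relating to the first year of the study will be extracted from these records". The window is a calendar year of the study, not a period counted from each person's answer.

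Under Participants, "In the first quarter of the first year, a baseline survey will be performed to assess the 3-month prevalence of back pain". The exclusion there is "having applied for or used medical rehabilitation services during the last 4 years", and the Abstract applies the same 4-year condition to eligibility for the first survey. Neither place gives the date from which the four years are counted back.

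The order of events is stated. According to the Abstract, "The sample will be drawn randomly from the registers of the GPI North" and of the second regional insurer. According to Recruitment, "After the sample has been drawn potential study participants will be contacted by post by the GPI". Reminders go out one, four and five weeks after the first mailing, and the week-4 reminder carries the full study material again. The only check by the insurer that is described after questionnaires come back concerns consent.

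Under Study design, the treated are those with back pain who complete a programme and the controls are those who do not take part. Neither definition refers to the questionnaire date. Baseline answers serve as predictors in the barrier analysis and as propensity score variables.

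**The concern.** A person can be free of any application at the draw, apply in the following weeks, and only then return the questionnaire. Nothing in the article removes that person or that application from the analysis.

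- **Barrier analysis.** The Background presents the prospective design as the study's advance over earlier cross-sectional work. For someone who has already applied, subjective need, intention, knowledge of the procedure and support from family or physicians are recorded after the event they are meant to predict. Associations could then run from application to answer. An application alone is enough to cause this; no treatment is needed.
- **Effectiveness analysis.** For someone who has already started a programme, baseline pain disability and the other propensity variables are values taken during or after treatment. Matching on them would remove part of the effect being estimated. This needs application, approval and start all to fall before the questionnaire is returned.

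**Working it through.** **1. The plan's own figures.** Inputs are from Sample size estimation and the Abstract.

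- Flow: 45,000 × 0.40 × 0.80 × 0.40 = 5,760; × 0.08 = 460.8; × 0.60 = 276.5. The stated 5,760 and 276 reproduce.
- Power for 276 against 828, standardised difference 0.2, two-sided 0.05: 0.2 / √(1/276 + 1/828) = 2.878, and Φ(2.878 − 1.960) = 0.82. The stated 0.82 reproduces and is not in dispute.

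**2. The dates side by side.**

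| Event | Stated timing | Section |
|---|---|---|
| Draw from registers | Before mailing; date not given | Abstract; Recruitment |
| Reference date of 4-year look-back | Not given | Abstract; Participants |
| Baseline survey | First quarter of year one | Participants |
| Reminders | Weeks 1, 4 and 5 after first mailing | Recruitment |
| Register window | Year one; first day not given | Intervention |

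The survey period lies inside the register window. Returns more than a month after first mailing are provided for.

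**3. How many could be affected.** The documents give no return dates, monthly rates or waiting times, so this is a range under assumptions. Let the draw and look-back be at week 0 of year one, all questionnaires return at week w, applications be spread evenly, and a fixed lag of L weeks separate application from programme start. Only applications up to week 52 − L then lead to a start within the year. Among the 276:

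- applied before return = 276 × w / (52 − L)
- started before return = 276 × max(0, w − L) / (52 − L)

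| Lag L | w = 4 | w = 6 | w = 9 | w = 13 |
|---|---|---|---|---|
| 0 | 21.2 / 21.2 | 31.8 / 31.8 | 47.8 / 47.8 | 69.0 / 69.0 |
| 4 | 23.0 / 0 | 34.5 / 11.5 | 51.8 / 28.8 | 74.8 / 51.8 |
| 8 | 25.1 / 0 | 37.6 / 0 | 56.5 / 6.3 | 81.5 / 31.4 |
| 13 | 28.3 / 0 | 42.5 / 0 | 63.7 / 0 | 92.0 / 0 |

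Each cell shows applied / started before return. With lags of 4 to 13 weeks, applications before return run from 23 to 92, a share of 8% (23/276) to 33% (92/276). The two counts move in opposite directions: at a given return week, a longer lag raises the share who had applied and lowers the share who had started. The no-lag row is an upper bound for starts, because a new case must apply, be approved and begin.

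**4. Power if early starters are removed.** At 1:3 matching, 244 rehabilitants give 0.77 and 207 give 0.70. Removing 31 leaves 245, so about 0.77. Removing the no-lag upper bound of 69 leaves 207, so 0.70. Removing none leaves 0.82.

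**The case against.** The strongest reply is that an extraction window is not an exposure definition. The article says which records are pulled, not that every year-one record is classed as treatment whatever its date. It also describes a sequence of survey first and follow-up afterwards, and calls the analysis prospective. Date rules for sorting register events could stand in the full protocol or analysis plan, which are not shown. The look-back might also be re-checked at the questionnaire.

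This limits what can be claimed: such persons *can* be counted, not that they *will* be. It does not remove the point. The window is stated in calendar time, it overlaps the survey period, and following it as written breaks the stated sequence.

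A reader might go further and infer that everyone who applied before answering contaminates the matched comparison, so that a quarter or more of the treated group is invalid. The documents do not support that. Someone who applied before answering but was treated afterwards still has a pre-treatment baseline pain score. The long lag that produces the highest applicant counts also implies that no one who applied after the draw had started treatment before return. Faster entry is most plausible through the simplified post-acute route, which the Background puts at about one third of all rehabilitation measures without giving its timing.

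**Conclusion.** The concern holds as a misaligned time zero. The stated register window contains the baseline period, the draw precedes mailing, and no rule orders events relative to the person's questionnaire. The harm falls mainly on the barrier analysis. For effectiveness it is confined to those who had started a programme before answering. They are probably few, so bias in the matched estimate is probably small.

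The size cannot be derived from the documents. The ranges are about 23 to 92 of 276 for applications before return, and 0 to about 31 for programme starts before return with an 8-week lag. No starts precede return with a 13-week lag, and about 69 is the upper bound with no lag. All of these rest on even application rates, one common return week and a draw at the start of year one. A draw after the start of the year would lower the applicant counts, because the look-back would catch earlier applications. A draw before it would put some applications outside the extracted year. The barrier analysis also includes applicants who are never treated, so for that analysis the share (8% to 33%) is more informative than the count.

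**What to change.** Set time zero at each person's questionnaire return date and state the reference date of the 4-year look-back. Then use a separate rule for each analysis:

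- **Barrier analysis:** count only applications dated after return, and exclude persons who applied earlier.
- **Effectiveness analysis:** count only programmes started after return, and exclude persons whose programme started earlier from both groups. Keep those who applied before but started after return, with a sensitivity analysis that excludes them. That check is useful because a pending application may make the intention and knowledge items near-proxies for treatment and so weaken propensity score overlap.
- **Reporting:** give the number of earlier applications and earlier programme starts.

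Dropping every early applicant from the effectiveness analysis is not recommended. It discards correctly timed treated cases and gives up power for little gain.

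The cost is recording return dates and requesting application and start dates in the extract already planned. This can still be done although recruitment has begun. The loss of rehabilitants from the effectiveness analysis should be small: power stays at 0.82 if no one started early and falls to about 0.77 if 31 did.
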